# Clinical background

In 2007 it was estimated that 33.2 million people were living with HIV and that there were 2.5 million new infections during that year. Discovering ways to prevent the transmission of HIV is of primary concern to health care authorities worldwide.

Numerous papers on the topic have been published over the past two decades to elevate HIV prevention awareness, especially in sub-Saharan countries.

In 2009, the US Government (USAID) reported that scaling up male circumcision (MC) to reach 80 percent of adult and newborn males in 14 African countries by 2015 could potentially avert more than 4 million adult HIV infections between 2009 and 2025 and yield annual cost savings of US$1.4 - 1.8 billion after 2015, with a total net savings of US$20.2 billion between 2009 and 2025.

To date, there are over 38 million adolescent and adult males in Africa that could benefit from MC for HIV prevention. The challenge Africa faces is how to safely scale up a surgical procedure in resource limited settings.

The PrePex device was accepted for the World Health Organization (WHO) list of prequalified MC devices and was listed on 31 May 2013.

PrePex became the first medical device for adult MC to receive WHO prequalification as an alternative to the conventional surgical circumcision methods already recognized by WHO.

Voluntary Medical Male Circumcision (VMMC) is a one-time, low cost intervention that shown to reduce men’s risk of HIV infection by approximately 70 percent. The WHO recommends VMMC as part of a comprehensive package of HIV prevention services. The WHO prequalification of PrePex represents an unprecedented opportunity to further the safe and rapid scale up of voluntary medical male circumcision programs [Official statement by the Office of the U.S. Global AIDS Coordinator].

Up to date more than 7,500 MCs were performed using the PrePex device. Rwanda, Zimbabwe and Uganda have completed the WHO clinical roadmap, scientifically validating the safety, efficacy, acceptability and superiority (over dorsal slit, on both measures of time and safety) of PrePex, other countries such as Kenya, Botswana and Mozambique are currently conducting PrePex pilot studies.

A concern that was raised by WHO TAG consulting members regarding the potential acceptability of PrePex by men involved the potential of strong odor extraction from the necrotizing foreskin. PrePex researchers from Rwanda have assumed that there is a possible relation of the level of odor to the personal hygiene and foreskin washing technique. It is speculated that when a patient follows an appropriate washing technique of the foreskin while wearing the device, the odor before device removal (day 7) will be redundant and significantly lower than the odor of the foreskin of a patient that does not follow such washing instructions and technique. Providing scientific evidence of the direct relation between odor and personal hygiene will allow VMMC implementing bodies to create a comprehensive and effective PrePex personal hygiene protocol and increase acceptability of the VMMC.

Rwanda has a national plan to offer a voluntary MC program to 2 million adult men in 2 years as part of a comprehensive HIV prevention strategy. To achieve this goal, the government launched a national study, based on the WHO Framework for Evaluation of Adult MC Devices, to assess the safety, efficacy and supremacy of the PrePex device when compared to surgical circumcision.

**Safety Study:**

The first safety study of PrePex was conducted in Rwanda between March 2010 to Dec 2010 in three steps: 5 subjects for pre-safety/feasibility, which went through self detachment of the foreskin and demonstrated the capability for foreskin self detachment; a pivotal phase of 50 subjects; a final extension phase of another 50 subjects.

A formal study report of the results of the first 40 subjects was accepted to CROI, a reputable infectious disease conference in Boston, USA. A report of the first pivotal study (full 50 subjects) was issued, the following represents a summary of the clinical experience.

**Study Summary:**

A study of 50 male subjects aged 18 to 35 years was conducted to assess the safety and efficacy of PrePex, a new medical device that has the potential to facilitate rapid scale-up of male circumcision (MC) in resource limited settings. The device is explored in the context of the Republic of Rwanda’s national scale-up plan, which calls for circumcision of 2 million adult men in 2 years as part of its national HIV prevention strategy.

The pivotal study was preempted by a feasibility stage that included 5 subjects. While this report focuses on the pivotal stage, it also offers insights from the feasibility study that lead to the methods and techniques in the pivotal stage.

The procedure was performed with no anesthesia. There were no cases of bleeding. There was no need for suturing. There were no clinical adverse events related to the procedure (from device Placement to device Removal) and there were no device-related incidents. Following device removal, there was 1 mild adverse event that was resolved with minimal intervention. Subjects returned to their daily routine shortly after Placement and immediately after removal of the device. The median time for complete healing[[1]](#footnote-2) was 21 days post device removal and the average was 25.3 days post device removal.

It was concluded that the tested device is safe. Furthermore, 100% of the subjects achieved the endpoint of complete circumcision, indicating device efficacy.

**Comparative Study:**

Background: This study was designed to compare a new non-surgical device with surgical MC, verifying the viability of the MC scale-up goal.

Methods: Prospective, randomized, controlled trial in Rwanda in which PrePex device was used for non-surgical MC and the dorsal-slit method (according to *WHO MC Manual v2.5C 08 MC under local anesthesia*) for surgical MC (ratio 2:1). Subjects were healthy adult male volunteers aged 21-54. The primary endpoint, set by WHO, was total MC procedure time.

Findings: Out of 217 eligible subjects, 144 randomized to PrePex/non-surgical arm and 73 to the surgical arm. All subjects were circumcised in 10 working days. Non-surgical MC was bloodless, without anesthesia, sutures or sterile setting, and with mean procedure time of 3.1 minutes skin to skin) - significantly shorter compared to mean surgical procedure time (15.4 minutes skin to skin) (p<0001). There were no device-related incidents.

Conclusion: PrePex MC is superior to surgical MC as measured by procedure time. Rwanda selected PrePex for national scale up.

**Cohort Nurses Study:**

Background: This study represents the third and final clinical evaluation of PrePex device, performed in mid 2011 in Rwanda, based on World Health Organization suggested framework for evaluating Male circumcision devices, following the validation of safety, efficacy and supremacy over surgical circumcision performed by surgeons. The national goal in Rwanda is to offer voluntary male circumcision to 2 million men within 2 years to decrease HIV incidence, and this can only be achieved if nurses can safely conduct the procedure, as there are not enough physicians. It was assumed that the Adverse Event rate will be below 2%.

Methods: Rwanda National Ethics Committee approved the study. The study was conducted in Rwanda Military Hospital, Kigali Rwanda, between July 2011 to September 2011. 10 nurses with no previous knowledge on PrePex device were trained for 3 days on PrePex circumcision method. 590 healthy adult male volunteers were enrolled in the study and distributed between 5 teams of 2 nurses each. The device works by stopping flow of blood to the distal foreskin, leading to necrosis of the tissue, which is removed, along with the device, after 7 days in situ. The Placement and Removal procedures were bloodless, required no injected anesthesia, no sutures and no sterile settings. AE data, severity and relation to device was gathered throughout weekly visit for 8 weeks follow up, post Removal.

Results: All 590 male subjects achieved the endpoint of complete circumcision with glans fully exposed. There were 2 device related moderate AE (rate of 0.34%) including 1 case of bleeding 6 hours post removal that required 1 suture and 1 case of erroneous placement that partially disturbed urination flow, and required replacement. There were 2 non-device related AE (rate of 0.34%), both moderate, including 1 subject self removal and 1 subject partial removal of the device, contrary to specific instructions. All AE were easily resolved with simple intervention.

Conclusions and Recommendations: The study statistically demonstrated that circumcision performed by nurses when using PrePex device is safe and effective. The procedure was bloodless and required no injected anesthesia, no sutures and no sterile settings (only standard consultation room). The device is officially approved for use in Rwanda. PrePex has the potential to facilitate rapid, safe, MC scale-up programs for HIV prevention by nurses, an imminent need in Sub Saharan Africa where physicians are a limited resource.

Overall, more than 5,900 PrePex procedures were conducted by June 2013 in Rwanda, where 1,900 procedures were performed in the frame work of clinical studies.

This clinical study will include the following objectives:

- To compare the different odor levels when examining 3 arms with identical personal hygiene but different foreskin hygiene techniques
- To determine a detailed and validated foreskin cleaning procedure protocol, that will ensure low odor without compromising safety

To compare the different perception of the subject’s partner relating to the odor when examining 3 arms with identical personal hygiene but different foreskin hygiene techniques.

This protocol describes the endpoints and methods of assessing those objectives.

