**Primary Objectives:**

- Safety - To determine the adverse events rate per foreskin cleaning technique per study arm
- Efficacy - To compare the different odor levels when examine 3 arms of patients undergoing PrePex circumcision with same personal hygiene and with different foreskin hygiene techniques

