**Secondary Objectives**

- To determine an absolute odor level per each arm
- To determine a penis cleaning procedure guidelines safety and efficacy
- To compare the different perception of the subject’s partner relating to the odor when examine 3 arms of patients undergoing PrePex circumcision with same personal hygiene and with different foreskin hygiene techniques.

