**Secondary Endpoints:**

- To determine the odor levels between 3 arms in order to assess patients' acceptability
- To determine a penis cleaning procedure guidelines safety and efficacy to be a part of the PrePex normal routine program
- To assess the patient's partner perspective of the smell to evaluate their acceptability.

4. Selection and Withdrawal of Subjects

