## 8.3 Statistical analysis

**Sample size:**

The intention is to obtain at least 100 evaluable subjects under Rwanda ethical responsibility (RNEC), determining to use the most deducted calculation setting and to maintain allocation ratio of 1:1:1 between the 3 study arms (33 per arm).

A sample size for the study was determined based on the two-sample t-test. In order to detect an effect size of 0.7 (Cohen's D) with 80% and at and a 5% level of significance between any two groups a sample size of 33 subjects is required. In the study each subject will have a smell test repeated by three different smellers this will be in order to examine the variability in odor sensation between different clinicians. Given this design and the three groups that will be compared, a statistically more powerful model (repeated measures ANOVA) is used instead of a t-test, and thus the study will be appropriately powered.

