## 8.3.1 General Considerations

The primary analysis will be performed on an intent-to-treat basis. Per-protocol analysis also will be performed as a secondary analysis. The required significance level of findings will be equal to or lower than 5%. All statistical tests will be two-sided. Where confidence limits are appropriate, the confidence level will be 95%.

All data will be presented via descriptive statistics. Binary data such as adverse events success/fail criteria will be presented as a count and percentage together with an exact 95% confidence interval. Adverse event rates will be compared descriptively with the reported rates of similar treatments. Continuous data will be represented by a mean, standard deviation, median, minimum and maximum together with 95% confidence intervals for the means.

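### The stated aim of a validated cleaning procedure that does no harm claims more about safety than 33 men per arm, sized on odor alone, can support

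*Protocol*

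**What the plan says.** The Study Synopsis and section 1 (Clinical background, closing list of objectives) both give this aim: "To determine a detailed and validated foreskin cleaning procedure protocol, that will ensure low odor without compromising safety". Section 3, Secondary Endpoints, gives the intended use: "To determine a penis cleaning procedure guidelines safety and efficacy to be a part of the PrePex normal routine program".

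Elsewhere the safety aim is worded more modestly. The second list of primary objectives in the synopsis has "Safety - To determine the adverse events rate per foreskin cleaning technique per study arm". Section 2 and the synopsis list, as a secondary objective, "To determine a penis cleaning procedure guidelines safety and efficacy".

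On size, the synopsis and section 8.3 say "A sample size for the study was determined based on the two-sample t-test" and "In order to detect an effect size of 0.7 (Cohen's D) with 80" per cent power at the 5% level, and they "maintain allocation ratio of 1:1:1 between the 3 study arms (33 per arm"). No safety quantity enters the calculation.

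On analysis, the synopsis and sections 8.3 and 8.3.1 plan counts and percentages with exact 95% confidence intervals for binary data such as AEs. They then state: "Adverse event rates will be compared descriptively with the reported rates of similar treatments". No other comparison of AE rates is named.

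**The concern.** To call a procedure validated and free of any cost in safety is to conclude that there is no harm. Such a conclusion needs an AE rate, or an excess over control, that the data rule out. This trial was sized for odor, so whatever it rules out on safety is a by-product of that choice.

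The procedure is meant for routine use, and section 1 describes a national plan to offer circumcision to 2 million men. If the arms show few or no AEs, the stated aim invites the report to say that safety was shown, although the data would still be compatible with an AE rate well above those quoted in section 1.

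The named comparison adds to this. Arm 1 is a randomised control followed in the same way at the same site, yet the text points only to outside rates.

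**Working it through.** **1. The plan's own figure.** A two-sample t-test with d = 0.7, two-sided 5% and 80% power needs n = 33.02 per group by the noncentral t distribution, and power at 33 is 79.97%. The stated 33 therefore reproduces for odor.

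**2. Benchmarks from section 1, Cohort Nurses Study.** There were 590 men, 2 device-related AEs (0.34%) and 2 non-device-related AEs (0.34%). Combined: 4/590 = 0.68%. The assumed rate was below 2%.

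**3. What one arm can exclude.** The exact (Clopper-Pearson) two-sided 95% upper limit with no events is 1 − 0.025^(1/n).
- 0/33: 1 − 0.025^(1/33) = 10.6%
- 1/33: 97.5th percentile of Beta(2, 32) = 15.8%
- 0/66 (both syringe arms pooled): 1 − 0.025^(1/66) = 5.4%

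Against the benchmarks: 10.58/2 = 5.3, and 10.58/0.68 = 15.6.

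**4. How often an arm would be clean.** P(no events in 33) = (1 − p)^33. The true rates p are assumptions, the first two being the benchmark figures.

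| True AE rate | P(0 of 33) |
| --- | --- |
| 0.68% | 80% |
| 2% | 51% |
| 5% | 18% |
| 10% | 3% |

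**5. What a between-arm comparison can exclude.** For 0/33 versus 0/33 the Wilson upper limit in each arm is z²/(n + z²) = 3.84/36.84 = 10.4%. The Newcombe 95% interval for the difference is therefore −10.4 to +10.4 points. Using the concurrent control does not remove the limit, but it does make the comparison like for like.

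**6. Where the limit ends.** For illustration only, since the protocol plans no such test: with a true 25% in a syringe arm, a two-sided 5% Fisher test at 33 versus 33 would be significant in 81% of trials if the control rate were 0.68%, and in 71% if it were 2%. A very large excess would probably be detected.

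**The case against.** Much can be said for the plan. Safety is to be described, not tested. The synopsis already has a purely descriptive objective, the AE rate per technique per arm, and exact 95% intervals are planned, so a 0/33 result should appear with its 10.6% limit beside it. Section 2 does not repeat the strong wording. The absence of a safety margin or decision rule is not in itself a fault, because a protocol may leave that to the statistical analysis plan, which is not at hand. All of this stands, and it is why the point is minor. What it does not answer is the mismatch: two places state a no-harm aim and a third intends routine use, while the design supports a description. A later plan can add intervals, but not information to 33 men per arm.

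Three stronger readings are tempting and should not be drawn.

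- *That no excess would be the expected result even under real harm.* The chance that a syringe arm shows no more AEs than control is 38% for 2% versus 5%, 12% for 2% versus 10%, 4% for 5% versus 20% and 0.8% for 2% versus 20% (independent binomials, 33 per arm; assumed rates). Real harm would usually leave some numerical excess. The difficulty is that an interval from this size could not exclude a moderate one.
- *That the safety comparison is underpowered against a 20% limit on missed effects.* The 80% power is set for odor. The protocol plans no between-arm AE test and sets no power for safety.
- *That a clean arm leaves open 31 times the known rate.* That ratio uses device-related events only. Section 9.2 records related and unrelated AEs, so the combined 0.68% is the closer figure. Even this is rough: the cohort followed men for 8 weeks after removal, all four of its AEs were moderate, and this trial has mild grades, sets some expected side effects aside and requires no follow-up after removal.

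**Conclusion.** The point holds as a mismatch between the wording of an aim and the information in the trial. A clean arm of 33 leaves a true AE rate of up to 10.6% open, and two clean arms leave an excess of up to 10.4 points open. These limits follow from the arm size alone and need no assumed AE rate. The ratios of about 5 and 15 to 16 rest on a cohort with different AE definitions and follow-up, so they give only an order of size.

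The documents do not say that the absence of an excess will be reported as safety. They leave that inference open by stating the aim as they do. The sample size is right for odor and the planned exact intervals are sound. Severity is minor.

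**What to change.** - In the synopsis and section 1, replace the aim with one in line with the descriptive safety objective in the synopsis: compare odor between arms and describe the AE rate of each cleaning technique. Drop the word validated and the closing clause on safety. Reword the matching secondary endpoint in section 3 in the same way.
- For each syringe arm, report the AE rate with the exact 95% interval already planned, and add the difference from Arm 1 with its 95% interval. The comparison with outside rates can stay as context, with its differences in definition and follow-up stated.
- Word the safety conclusion as what is excluded. For example, no events in 33 men exclude rates above 10.6%.
- State that the absence of an observed excess will not be reported as showing safety.

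The cost is a few lines of text and one more interval per syringe arm from data already collected, with no more patients. The downside is a more modest safety claim.

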# 2. STUDY OBJECTIVES AND PURPOSE

**Primary Objectives:**

- To compare the different odor levels when examine 3 arms of patients undergoing PrePex circumcision with same personal hygiene and with different foreskin hygiene techniques.

**Secondary Objectives**

- To determine an absolute odor level per each arm
- To determine a penis cleaning procedure guidelines safety and efficacy
- To compare the different perception of the subject’s partner relating to the odor when examine 3 arms of patients undergoing PrePex circumcision with same personal hygiene and with different foreskin hygiene techniques.

## 2.1 Clinical Trial Design

Assessing Odor Level when Using PrePexfor HIV Prevention: A Prospective, Randomized, Open Label, Blinded Assessor Trial to Improve Uptake of Male Circumcision.

3. STUDY ENDPOINTS

**Endpoints:**

**Primary Endpoint:**

- The primary endpoint is to assess the different odor levels by evaluating 3 arms of patients with different foreskin hygiene techniques.

**Secondary Endpoints:**

- To determine the odor levels between 3 arms in order to assess patients' acceptability
- To determine a penis cleaning procedure guidelines safety and efficacy to be a part of the PrePex normal routine program
- To assess the patient's partner perspective of the smell to evaluate their acceptability.

4. Selection and Withdrawal of Subjects

## 4.1Source of Subjects and Enrollment

Male subjects that are voluntary scheduled for circumcision. Only subjects who have signed the last version of an Independent Ethical Committee (IEC)/Institutional Review Board (IRB) approved Informed Consent Form (ICF) and meet all of the eligibility criteria listed below will be qualified for enrollment. The study will recruit at least 100 evaluable subjects who will complete the protocol procedure /treatment and the follow-up schedule.

## 4.2 Eligibility Criteria

**Eligibility Criteria:**

**Inclusion Criteria:**

- Ages – 21 to 49 years
- Subject wants to be circumcised
- Uncircumcised
- Able to understand the study procedures and requirements
- Agrees to participate in either arm and to follow hygiene instructions
- Agrees to have Independent blinded smell reviewers in the same room on Removal visit
- Agrees that his partner will be interviewed via telephone
- Agrees to abstain sexual intercourse for 6 weeks post device removal
- Agrees to abstain from masturbation for 2 weeks post device removal
- Agrees to return to the health care facility for follow-up visits (or as instructed) after his circumcision for a period of 1 week
- Subject able to comprehend and freely give informed consent for participation in this study and is considered by the investigator to have good compliance for the study
- Subject agrees to anonymous video and photographs of the procedure and follow up visits.

**Exclusion Criteria:**

- Active genital infection, anatomic abnormality or other condition, which in the opinion of the investigator prevents the subject from undergoing a circumcision
- Subject with the following diseases/conditions: phimosis, paraphimosis, warts under the prepuce, torn or tight frenulum, narrow prepuce, hypospadias, epispadias
- Known bleeding / coagulation abnormality, uncontrolled diabetes, by questionnaire
- Subject who have an abnormal penile anatomy or any penile diseases
- Subject that to the opinion of the investigator is not a good candidate
- Subject does not agree to anonymous video and photographs of the procedure and follow up visits.

